#### Intervention - home telemonitoring

The Intel Health Guide is a U.S. Food and Drug Administration-approved device that is placed in the patient's home and connected to the health system via broadband Internet or 3G network. This device has video monitoring that allows real-time, face-to-face interaction with the provider team. Peripheral devices can be attached to measure blood pressure and pulse, oxygen saturation via pulse oximetry, glucose level via glucometer, and weight. The device incorporates a programmable, patient condition-specific touch-screen questionnaire for daily progress reporting.

The initial data collected is downloaded to the Web-based Intel Health Suite for access by the provider group via the Internet from any PC-based computer. Each patient has an individualized protocol of daily assessment questions and biometric parameters with predetermined action thresholds that are developed, revised, and monitored by the care team. An overview of the health guidelines is provided in Table 2. An example of one such parameter is the daily measurement of weight for patients with heart failure. If the weight falls outside of preset minimum or maximum values, the Intel Health Suite highlights the abnormality for the monitoring provider group.

**Table 2 T2:** Intel Health Guide health guidelines (general)

Measurement	Normal range
Systolic blood pressure	<140 mm Hg

Diastolic blood pressure	<90 mm Hg

Pulse oximetry	>88%

Weight gain of 2 pounds/day	<2 pounds a day

Weight gain of 5 pounds/week	<5 pounds gain a week

Fasting blood sugar	80-120 mg/dL

Heart rate	60-100 beats/min.

The implementation and monitoring of the Intel Health Guide involves a team of individuals. GE Healthcare installs the system, and a clinical assistant educates the patient on how to use the Intel Health Guide and serves as a contact for questions on the device or peripherals. The protocols are determined and loaded into the device by a registered nurse (RN) and modified by a nurse practitioner (NP) overseeing the care. The patient's primary care physician oversees the overall medical care of the telemonitoring through input from the RN or NP. One RN oversees the 100 subjects on the study every day.

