#### Assessments

All patients enrolled in the study will participate in three face-to-face visits and two phone calls. The initial visit, 6-month visit, and 12-month visit will use instruments to measure functional status, quality of life, cognition, mood, self-reported outcomes, attitudes, behaviors, and compliance. At the initial visit, the patient's Mayo current visit information and family history will be collected. At 3 months and 9 months, the study team will call the patient for descriptions of quality of life and mood. If the results indicate a risk to the patient, the patient's primary care physician will be contacted. Specifically, if the patient health questionnaire PHQ-9 indicates depression (score >14)[5], or the Kokmen Short Test of Mental Status indicates memory loss or changes of functional status (≤29)[6], this finding will be reported to the primary care physician.

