#### Outcomes measurement

The primary outcomes are hospitalizations, ED visits, and the composite outcome of hospitalizations and ED visits. Olmsted County has two primary medical centers, and all listed outcomes can be collected through the Rochester Epidemiology Project. Patient self-reports will also be used to capture care provided outside of Olmsted County, and these events will be verified by the study team. In addition, Medicare claims data will be reviewed for hospitalizations and associated costs. In practical terms, almost all patients who visit PCIM preferentially use Mayo facilities for ED and hospital care. These measures will be obtained from the medical record.

An economic analysis will be performed comparing usual care and home telemonitoring, including total non-elective care costs based on reimbursement from Medicare, Medicaid, and private insurance. Cost analysis will also use standard Centers for Medicare and Medicaid Services (CMS) costing information and reimbursement information. This will include inpatient, outpatient, and skilled nursing facility stays, and home healthcare adjusted for CMS Hierarchical Condition Codes and regional variation as well as all direct and indirect costs of the telemonitoring.

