The major limitation is the lack of blinding inherent with two disparate groups of patients. This could lead to the Hawthorne Effect and lead to bias. It will not be practical to blind the providers or the patients receiving home equipment and constant monitoring at home. The limitations imposed will be mitigated despite the lack of blinding. Specifically, hospitalizations and ED visits as the primary outcome should occur regardless of arm or treatment and are not subjective measures. There is the potential for recall bias on self-reported outcomes; however, the primary outcomes should be captured by the medical record in nearly all cases.

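### Medicare claims are assigned to hospitalizations and costs but not to ED visits, so an out-of-county ED visit without admission is left to unblinded self-report alone

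*Protocol article*

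**What the plan says.** Outcomes measurement defines the endpoints: "The primary outcomes are hospitalizations, ED visits, and the composite outcome of hospitalizations and ED visits". It then names the sources.

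- For care in Olmsted County, "all listed outcomes can be collected through the Rochester Epidemiology Project", supported by the medical record.
- For care elsewhere, "Patient self-reports will also be used to capture care provided outside of Olmsted County, and these events will be verified by the study team".
- As a further layer, "Medicare claims data will be reviewed for hospitalizations and associated costs".

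The next paragraph of that section plans an economic analysis based on payer reimbursement (Medicare, Medicaid and private insurance). It includes outpatient care but is not given a role in finding events.

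Study design states that patients and providers know the allocation and that only the analysis is blinded. Under Assessments, "All patients enrolled in the study will participate in three face-to-face visits and two phone calls". In the telemonitoring arm, "One RN oversees the 100 subjects on the study every day". The limitations paragraph of the Discussion concedes that "There is the potential for recall bias on self-reported outcomes", and adds that the medical record should hold the primary outcomes in nearly all cases.

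**The concern.** The claims review would find events in both arms without depending on what a patient remembers or chooses to mention. As written, it serves one of the two components. A hospital stay outside the county that the patient never mentions can still be found in claims. An ED visit outside the county that ends in discharge has no such second route.

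Verification does not close this gap. It removes false reports, so it improves specificity. The weakness is in sensitivity.

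The trial is unblinded and the arms differ in how much contact they have with clinical staff, so completeness of reporting could differ by arm. A difference in capture would then enter the treatment comparison. In the Cox analysis, a missed ED visit followed by a later admission would also date the first event too late.

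**Working it through.** **1. Sources set side by side (Outcomes measurement)**

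| Event | In Olmsted County | Outside the county |
|---|---|---|
| Hospitalization | Rochester Epidemiology Project, medical record | Verified self-report; Medicare claims |
| ED visit without admission | Rochester Epidemiology Project, medical record | Verified self-report only |

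Only the lower right cell is exposed.

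**2. The plan's own figures**

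The log-rank calculation under Sample size reproduces closely. HR = ln(0.380)/ln(0.285) = 0.771, which needs 464 events (Schoenfeld) or 469 (Freedman) against the stated 463. The present point does not contest it.

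The relevant figures are in Table 3. At 100 per group, control rate = intervention rate / (1 − drop):

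- Hospitalized: 27.1 / (1 − 0.425) = 47.1%
- ED visit or hospitalization: 38.2 / (1 − 0.361) = 59.8%
- ED visit without hospitalization: 59.8 − 47.1 = 12.7 points, and 12.7 / 59.8 = 21% of control patients with an event
- The same in the intervention arm: (38.2 − 27.1) / 38.2 = 29%

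The other rows of Table 3 give about 20% in the control arm and 24% to 27% in the intervention arm.

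**3. Shift in the composite, by share of first events**

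The article gives no out-of-county share, so all of the following inputs are assumed. Let s be the share of first events that are out-of-county ED visits without admission, with capture of 90% in telemonitoring and 60% in usual care.

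Observed HR / true HR ≈ [1 − s(1 − 0.9)] / [1 − s(1 − 0.6)]

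- s = 2%: 0.998 / 0.992 = 1.006
- s = 5%: 0.995 / 0.980 = 1.015
- s = 10%: 0.990 / 0.960 = 1.031

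Reversing the capture rates moves the ratio by about the same amount the other way. The formula treats a missed first event as lost, although a later captured event would keep the patient as an event at a later date. The upper values of s are also generous. Measured against patients with an event, 10% would be 10 / 21 = 48% of the ED-only patients.

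**4. Shift under no true effect, by share of ED-only patients**

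Take 100 per arm, a composite rate of 59.8% and an ED-only rate of 12.7%. Let s be the out-of-county share of ED-only patients and d the difference between arms in the fraction missed. Then lost = 0.127 × s × d, and HR = ln(1 − 0.598 + lost) / ln(1 − 0.598). The rejection rate uses a two-proportion normal approximation.

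| s | d | Lost per 100 | Apparent HR | Two-sided rejection rate |
|---|---|---|---|---|
| 2% | 50% | 0.13 | 0.997 | 5.0% |
| 5% | 50% | 0.32 | 0.991 | 5.0% |
| 10% | 100% | 1.27 | 0.966 | 5.4% |
| 20% | 100% | 2.54 | 0.933 | 6.5% |

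These rows put the loss in telemonitoring. With the loss in usual care the HR is the reciprocal, for example 1 / 0.966 = 1.035.

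**5. Against the trial's precision**

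Table 3 at 100 per group implies 59.8 + 38.2 = 98 patients with an event, so the standard error of log HR is about 2/√98 = 0.20. The largest factor in step 3 gives ln(1.031) = 0.03, or about 0.15 standard errors.

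**6. ED visits on their own, and total counts**

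Here an admission does not stand in for a missed ED visit. If a share s of counted visits is exposed and the missed fraction differs by d, the ratio of mean counts under no effect is 1 − s × d:

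- s = 5%, d = 50%: 0.975
- s = 10%, d = 100%: 0.90

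The article gives no ED visit rate, so this cannot be turned into an error rate.

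**The case against.** The strongest reply is that this is a condensed article and that the claims review is an added layer on top of the local record and verified self-report. The sentence does not exclude ED claims, and the full protocol may say which claim types are extracted. That lowers the severity. Still, the sentence states what the claims are for and leaves out one primary component.

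Four stronger readings are tempting, and the document does not support them.

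- **Half of the composite is affected.** Table 3 puts ED-only patients at about a fifth of control patients with an event, and only their out-of-county part is exposed. A patient who is also admitted is still identified.
- **No source exists that treats the arms alike.** Outpatient reimbursement data are planned for both arms. They are simply not assigned to finding events.
- **Telemonitoring contact biases capture in a known direction.** All patients have the same visits and calls. The article describes device questionnaires and nurse contact when alerts arise, but not daily questions about ED use, and it does not say these contacts feed the outcome data. A difference by arm is possible but assumed.
- **The Discussion contradicts itself.** It claims capture by the record in nearly all cases, not all, and these visits belong to the remainder that it concedes.

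The expectation of few outside visits also stands in part. Outcomes measurement says that almost all patients in the internal medicine practice prefer the institution's facilities, and the Discussion describes a largely closed local system. Neither gives a figure. The first statement does not mention the family medicine patients, who are also enrolled.

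**Conclusion.** The concern holds as a low-severity gap in ascertainment. As the article assigns its sources, an ED visit outside the county without admission reaches the primary data only if an unblinded patient reports it.

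For the composite the effect is probably small and its direction unknown. The hazard ratio shifts by a factor of about 1.006 to 1.031 under the capture rates in step 3, and the type I error stays near 5% unless both the outside share and the difference in reporting are large. ED visits as a separate primary outcome and the secondary t-test on total visits are more exposed. All of these sizes rest on assumed out-of-county shares and assumed differences in reporting, because the article gives neither.

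**What to change.** In Outcomes measurement, extend the claims sentence so that it names emergency department visits alongside hospitalizations and costs. Add that ED visits identified from claims count as events in both arms, whether or not the patient reported them.

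This is one further extraction from claims already being reviewed. The cost is some extra event review. Patients without Medicare claims stay uncovered, which matters somewhat in a trial that enrols from age 60.

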### Sample size

Using an alpha value of 0.05 and a power of 80%, the power calculations were derived from an estimated 76% event rate of hospitalizations and ED visits in 2 years in the high-risk group. Using a time-to-event approach with a 25% reduction when the sample size in each group is 352, with a total number of events required, E, of 463, a 0.050 level two-sided log-rank test for equality of survival curves will have 80% power to detect the difference between a Group 1 proportion π_1 _at time t of 0.380 and a Group 2 proportion π_2 _at time t of 0.285 (a constant hazard ratio of 0.771); this assumes no dropouts before time t. Using 100 patients in each group with a yearly hospitalization/ED rate of 38.2%, we will be able to detect a 36.1% decrease in combined outcomes. Table 3 below reflects the changes with different size groups.

**Table 3 T3:** Sample sizes for hospitalizations and emergency department visits

Sample size	% hospitalized in intervention	% with ED/hospitalization in intervention
100	27.1 (42.5% drop)	38.2 (36.1% drop)

150	30.7 (34.8% drop)	42.1 (28.6% drop)

200	32.9 (30.1% drop)	44.4 (24.6% drop)

250	34.4 (27.0% drop)	46.0 (21.9% drop)

300	35.5 (24.6% drop)	47.2 (19.9% drop)

350	36.4 (22.7% drop)	48.1 (18.3% drop)

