## Methods/Design

### Study design

This multi-site, randomized controlled trial of home telemonitoring or usual care will take place in the four sites of the outpatient practice of Mayo Clinic's Division of Primary Care Internal Medicine (PCIM) in the Department of Family Medicine (FM) in Rochester, Minn. and nearby Kasson, Minn. The Mayo Elder Risk Assessment (ERA) Index will be used to randomly assign 200 high-risk patients to home telemonitoring or usual care (100 patients per intervention). Patients will be followed for 1 year after enrollment. Patients in the Rochester practice will be block-randomized as a single entity, and the patients in the Kasson practice will be block-randomized as a second entity. Subjects and providers will not be blinded to the allocation of the intervention, but analysis will be blinded to the allocation type.

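### The planning proportion of 0.380 appears to be a two-year 76% cut in half, which a first-event proportion does not allow, and the sample-size section mixes several control rates that must be reconciled

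*Protocol article*

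**What the plan says.** The Sample size section of the protocol article derives its power calculation from "an estimated 76% event rate of hospitalizations and ED visits in 2 years in the high-risk group". It continues "Using a time-to-event approach with a 25% reduction", with a Group 1 proportion "at time t of 0.380" and a Group 2 proportion "at time t of 0.285". It reports a constant hazard ratio of 0.771, 463 events and 352 patients per group, with no dropout, and states that "a 0.050 level two-sided log-rank test for equality of survival curves will have 80% power". It does not define t, does not say whether the proportions are with or without an event, and does not say how 0.380 was obtained.

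Under Study design the horizon is fixed: "Patients will be followed for 1 year after enrollment". The same section sets enrolment at 100 per group.

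The sample-size text then justifies 100 per group with a yearly composite rate of 38.2% and a detectable decrease of 36.1%. In Table 3, the row for 100 shows 38.2% as the rate in the intervention arm after a 36.1% drop.

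**The concern.** The step from 76% over two years to 0.380 in a one-year trial looks like division by two. The proportion with a first event accumulates as 1 - S(t), so its one-year value is half the two-year value only if the hazard rises steeply in the second year. Nothing in the document suggests that.

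The baseline matters because this is the only fully specified log-rank calculation for the composite outcome. It sets the hazard ratio, the events and the number per group for the 25% scenario. The section also carries other figures that look like control rates and do not agree with 0.380 or with each other. A reader therefore cannot tell which usual-care rate the trial expects, or whether 80% power for the stated 36.1% drop is right.

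**Working it through.** **Inputs.** From the Sample size section: 76% at 2 years; 0.380 and 0.285; 25% reduction; two-sided alpha 0.05; 80% power; HR 0.771; 463 events; 352 per group; no dropout; yearly rate 38.2%; drop 36.1%; Table 3. From Study design: 1 year of follow-up, 100 per group.

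**1. Reproducing the stated figures.** Schoenfeld events = 4(1.96 + 0.8416)²/(ln HR)² = 31.40/(ln HR)².
- Read as event-free proportions: HR = ln(0.380)/ln(0.285) = 0.771. Schoenfeld gives 463 events, as stated; Freedman gives 469. The number per group is events/(2 - 0.380 - 0.285) = events/1.335, about 347 (Schoenfeld) or 352 (Freedman, rounded up). The stated figures are recovered.
- Read as event proportions: HR = ln(0.715)/ln(0.620) = 0.702. Events = about 250 (Freedman 256). The number per group is events/(0.380 + 0.285), about 376 (Freedman 385).
- On the event reading, 352 per group would yield 704 × 0.3325 = 234 events, so 463 could not occur.

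The stated calculation therefore treats 0.380 and 0.285 as event-free. That means 62.0% of Group 1 and 71.5% of Group 2 have an event, which is not a 25% reduction in events.

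**2. Where 0.380 comes from.** 0.76/2 = 0.380 and 0.75 × 0.380 = 0.285, both exact.

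**3. Can 76% at two years be 38% at one year?**
- Taken literally: year-1 hazard -ln(0.62) = 0.478. In year 2, 0.38/0.62 = 61.3% of those still event-free would have an event, a hazard of 0.949. The hazard would have to double.
- Constant hazard: 1 - √(1 - 0.76) = 1 - √0.24 = 51.0%.
- 0.76 events per patient over two years, Poisson: 1 - exp(-0.38) = 31.6%.
- 0.380 as event-free: constant hazard leaves √0.24 = 49% event-free at one year. The curve reaches 38% only at 2 × ln(0.380)/ln(0.24) = 1.36 years.

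**4. The 25% scenario with event proportions entered as such.** HR = ln(1 - 0.75p)/ln(1 - p); number per group = events/(1.75p); Schoenfeld events:

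| One-year control p | Reduced to | HR | Events | Per group |
|---|---|---|---|---|
| 0.380 | 0.285 | 0.702 | 250 | 376 |
| 0.510 | 0.383 | 0.676 | 204 | 229 |
| 0.316 | 0.237 | 0.712 | 273 | 493 |

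For 0.510, Freedman gives 210 events and 236 per group.

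**5. Table 3.** Implied control rate = intervention rate/(1 - drop). Composite: 38.2/0.639 = 59.8% in the row for 100; 42.1/0.714 = 59.0% for 150; 48.1/0.817 = 58.9% for 350. Hospitalization alone: 27.1/0.575 = 47.1%. No time frame is given for these rates.

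**6. Power for 100 per group and a 36.1% drop.** Two proportions, p2 = 0.639p1, p̄ their mean: power = Φ{[(p1 - p2) - 1.96√(2p̄(1 - p̄)/100)] / √([p1(1 - p1) + p2(1 - p2)]/100)}.
- 38.2% to 24.4%: 56% (log-rank 57%).
- 51.0% to 32.6%: 76% (log-rank 77%).
- 59.8% to 38.2%: 87% (log-rank 88%).

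**The case against.** The halving is an inference. The text speaks only of time t and never calls 0.380 a one-year figure, an event proportion or half of 76%. This stands, and the point should be put as what the numbers indicate. The inference is still strong: the source is named, the ratio is exact, the horizon drops from two years to one, and no other origin is offered.

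A reader might also infer three stronger things that the document does not support:
- **That halving explains 463 events against about 250.** It does not. That gap comes entirely from using the proportions as event-free. The baseline accounts for the difference between 376 and 229 per group, and neither number is in the protocol.
- **That 51 of 100 usual-care patients should be expected to have an event.** Constant hazard is itself an assumption; the constant hazard ratio in the text means proportional hazards, not a flat baseline. Table 3 implies about 59-60%. If that is a one-year figure, the hazard falls from -ln(0.41) = 0.89 in year 1 to -ln(0.24/0.41) = 0.54 in year 2, and 51% is too low.
- **That the trial is too small because of the halving.** Moving from 0.380 to 0.510 lowers the number needed for the 25% scenario. The 100 per group rests on the separate 38.2%/36.1% statement and Table 3, not on the 352.

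If 76% is a count of events per patient, halving it gives a legitimate yearly rate, but 0.38 is then not the proportion that the calculation calls for.

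**Conclusion.** The point holds as an unsupported and unreconciled planning baseline. No reading of 76% over two years yields 0.380 as a one-year event proportion unless the hazard doubles in year 2. The candidates are 51.0% under constant hazard and 31.6% under Poisson counts. For the 25% scenario they give about 229 and 493 per group, so what 76% measures changes the answer more than twofold.

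Two further faults sit in the same section and would survive a change of baseline alone. The hazard ratio and events were calculated with 0.380 and 0.285 as event-free proportions. And 38.2% serves both as the yearly rate in the text and as the intervention-arm rate in Table 3, whose implied composite control rate is about 59-60%.

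The consequence for the trial as sized is that 80% power for a 36.1% drop cannot be confirmed: it is about 56%, 76% or 87% according to the baseline. These figures assume 1:1 allocation, two-sided 0.05 and no dropout.

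**What to change.** Rewrite the sample-size paragraph on a single baseline:
1. State whether 76% is the proportion of patients with at least one event or a count of events per patient.
2. State one sourced one-year usual-care proportion with a first hospitalization or ED visit. If only the two-year proportion exists, convert it by 1 - (1 - 0.76)^(1/2) = 0.51 and label constant hazard as an assumption.
3. Define t, label the proportions as event proportions, and enter them as such.
4. Rerun the 25% scenario. At 51.0% to 38.3% this gives HR about 0.68, about 204-210 events and about 229-236 per group.
5. Reconcile the 38.2% yearly rate, the 36.1% detectable drop and Table 3 with that baseline, and give the control rate and time frame in the table. Inserting 0.51 without this step would only add another conflicting rate.

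The cost is one rerun calculation, a reworded paragraph and a relabelled table. Enrolment does not change. The downside is that the stated detectable effect for 100 per group may become less favourable.

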**Methods/Design:**

Two-hundred patients with the highest 10% Mayo Clinic Elder Risk Assessment scores will be randomly assigned to one of two interventions. Home telemonitoring involves the use of a computer device, the Intel Health Guide, which records biometric and symptom data from patients in their homes. This information is monitored by midlevel providers associated with a primary care medical practice. Under the usual care scenario, patients make appointments with their providers as problems arise and use ongoing support such as a 24-hour nurse line.

Patients will have initial evaluations of gait and quality of life using instruments such as the SF-12 Health Survey, the Kokmen Short Test of Mental Status, and the PHQ-9 health questionnaire. Patients will be followed for 1 year for primary outcomes of hospitalizations and emergency department visits. Secondary analysis will include quality of life, compliance with the device, and attitudes about telemonitoring. Sample size is based on an 80% power to detect a 36% difference between the two groups. The primary analysis will involve Cox proportional time-to-event analysis. Secondary analysis will use t-test comparisons for continuous variables and the chi square test for proportional analysis.

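### The sample size text gives Table 3's intervention-arm rate (38.2%) as the yearly rate, and never states the control rate on which 80% power at 100 per group depends

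*Protocol article*

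**What the plan says.** The Study design section allocates patients to "home telemonitoring or usual care (100 patients per intervention". The size is justified in the Sample size section and summarised in the abstract.

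- The starting point is a two-year rate: "the power calculations were derived from an estimated 76% event rate of hospitalizations and ED visits in 2 years in the high-risk group".
- A log-rank calculation follows: 352 per group, 463 events, Group 1 proportion 0.380, Group 2 proportion 0.285, hazard ratio 0.771, described as a 25% reduction. Its test is specified as follows: "a 0.050 level two-sided log-rank test for equality of survival curves will have 80% power".
- The claim for the trial's actual size is that 100 per group, "with a yearly hospitalization/ED rate of 38.2%, we will be able to detect a 36.1% decrease in combined outcomes".
- In Table 3 the row for 100 reads "38.2 (36.1% drop" in the column for the percentage "with ED/hospitalization in intervention".
- The abstract says: "Sample size is based on an 80% power to detect a 36% difference between the two groups".

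Neither the text nor Table 3 names a control rate for the table.

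**The concern.** One number cannot be both the rate from which a 36.1% decrease is measured and the rate that remains after it. The sentence invites the first reading and Table 3 shows the second. The first reading is easy to fall into, because 38.2% almost equals the 0.380 given for Group 1 one sentence earlier.

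The detectable effect depends strongly on the control rate, and this sentence is the document's only justification for 100 per group. If the rate is near 38%, the 80% power claim fails by a wide margin. If it is near 59%, the claim holds. As the section stands, a reader cannot tell which applies.

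**Working it through.** **Inputs.** n = 100 per group, 1:1 (Study design); two-sided alpha 0.05 and 80% power (Sample size); 38.2% and 36.1% (Sample size text and Table 3); 0.380, 0.285, HR 0.771, 352 per group and 463 events (Sample size text). No dropout, as the protocol's log-rank calculation assumes.

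**Step 1: recover the control rate behind Table 3.** Implied control = intervention rate / (1 - drop). Each row is then tested with the continuity-corrected two-proportion formula at a 58.9% control rate:

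power = Φ{ (p1 - p2 - 1/n - 1.96·√[2p̄(1-p̄)/n]) / √[(p1(1-p1) + p2(1-p2))/n] }

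| n per group | Composite, intervention | Stated drop | Implied control | Drop from 58.9% | Power from 58.9% |
|---|---|---|---|---|---|
| 100 | 38.2% | 36.1% | 59.8% | 35.1% | 80.1% |
| 150 | 42.1% | 28.6% | 59.0% | 28.5% | 80.1% |
| 200 | 44.4% | 24.6% | 58.9% | 24.6% | 80.2% |
| 250 | 46.0% | 21.9% | 58.9% | 21.9% | 80.1% |
| 300 | 47.2% | 19.9% | 58.9% | 19.9% | 79.8% |
| 350 | 48.1% | 18.3% | 58.9% | 18.3% | 79.8% |

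All six composite rates reproduce at 80% power from 58.9%. The hospitalization column reproduces in the same way from 47.1% (79.9-80.2%). Only the drop in the 100 row is out of line: 1 - 38.2/58.9 = 35.1%.

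**Step 2: take the sentence as written.** p1 = 0.382 and p2 = 0.382 × (1 - 0.361) = 0.2441.

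- Continuity-corrected: (0.1379 - 0.0100 - 0.1285)/0.06485 = -0.01, power 49.6%.
- Uncorrected chi-square: (0.1379 - 0.1285)/0.06485 = 0.144, power 55.7%.
- Log-rank: HR = ln(1 - 0.2441)/ln(1 - 0.382) = 0.581; expected events = 100 × (0.382 + 0.2441) = 62.6. Schoenfeld: √62.6 × |ln 0.581|/2 - 1.96 = 0.185, power 57.3%. Freedman: √62.6 × (1 - 0.581)/(1 + 0.581) - 1.96 = 0.134, power 55.3%.

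Eighty percent power for this contrast needs 177 per group (191 with continuity correction). At 100 per group, solving for p2 at 80% power gives 0.194 to 0.207 across the four methods, a relative reduction of 46-49%.

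**Step 3: take Table 3's control rate, 58.9%.**

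| Contrast, n = 100 per group | Continuity-corrected | Chi-square | Log-rank (Freedman, Schoenfeld) |
|---|---|---|---|
| 58.9% vs 38.2% (35.1% drop) | 80% | 84% | 83%, 86% |
| 58.9% vs 37.6% (36.1% drop) | 82% | 86% | 85%, 87% |

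**Step 4: check the 0.380 in the same paragraph.** The text presents 0.380 to 0.285 as a 25% reduction in events: 0.285/0.380 = 0.75. The stated hazard ratio does not fit that. ln(0.380)/ln(0.285) = 0.771 treats both as event-free proportions; as event rates, ln(0.715)/ln(0.620) = 0.702. The event count shows the same. With 352 per group, event rates of 0.380 and 0.285 give 352 × 0.665 = 234 events. Event-free proportions give 352 × (0.620 + 0.715) = 470, and the Schoenfeld requirement at HR 0.771 is 463. So the stated HR and the 463 events belong to 62% and 71.5% with events, whereas the text describes 38% and 28.5%.

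**The case against.** The strongest reply is that this is a mislabelled number and not a power failure. If 38.2% is the intervention-arm rate, then 24.4% is not the design's alternative, and 50-57% does not describe the design. On the control rate that reproduces every composite rate in Table 3, 100 per group has 82-87% power for a 36.1% drop. That stands. A reader might infer from the sentence that the trial simply has 50-57% power; the documents do not support this, because the figure holds only if the 1-year control rate is about 38%.

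Three further limits also stand.

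- A reader might add a third control rate by converting 76% over two years at constant hazard, 1 - √0.24 = 51%. That figure is not in the document. Taking 0.380 as half of 76% is likewise an inference, since the text does not describe the step. The conflict on the page is between 0.380 and the roughly 58.9% implied by Table 3.
- The abstract gives no control rate, so it does not repeat the 38.2% error. It carries over only the rounded 36% and does not say that the difference is relative.
- Nothing in the document says how a null result would be interpreted, so a misreading of one is not something the text shows.

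The reply does not rescue the sentence. It gives the wrong rate and a drop that is one percentage point too large, and it omits the rate on which both depend. This is not detail left to a fuller document: the article prints the calculation, and prints it wrongly.

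**Conclusion.** The point holds as an error in the stated justification of sample size. The text puts Table 3's intervention-arm rate where a baseline belongs, and the control rates behind the table (about 58.9% composite, 47.1% hospitalization) are unstated and at odds with 0.380. The drop in the 100 row should be 35.1% if the control rate is 58.9%.

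Whether the trial has 80% power for a reduction of about 36% cannot be settled from the document: it does if the control rate is 58.9% and does not if it is about 38%. These results assume full one-year follow-up, a two-sided 5% test and, for the log-rank figures, proportional hazards. The 58.9% is inferred from the table, but the agreement of all six rows leaves little doubt that the table was built on it.

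**What to change.** State one 1-year control rate for the composite outcome, with its basis, and use it throughout the Sample size section and Table 3.

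- If it is 58.9%, replace the sentence with: *100 per group gives 80% power for 58.9% versus 38.2%, a 35.1% relative reduction.* Correct 36.1% to 35.1% in the 100 row, and add the control rates (58.9% composite, 47.1% hospitalization) to Table 3.
- If it is about 38%, state that 100 per group gives 80% power only for a relative reduction of about 46-49%, and about 50-57% power for 36%. Recompute Table 3 from that rate.
- In either case, say whether 0.380 and 0.285 are proportions with or without an event, and make the hazard ratio, event count and group size agree with that.
- In the abstract, give the corrected figure and call it a relative reduction.

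The cost is a few sentences and one table. Enrolment does not change. The only downside is that the stated detectable effect may become less favourable.
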